### 3.4. Discontinuation and Withdrawal Criteria

Patients have the right to voluntarily withdraw from participating in the clinical study at any time, regardless of the reason. Additionally, the investigator has the authority to discontinue a patient's participation in the study.

Reasons for withdrawal from the clinical study may include, but are not limited to, the following:

- Withdrawal of consent by the study subject
- Medical conditions deemed to jeopardize the safety of the patient if the study continues
- When discontinuation of participation is in the best interest of the patient
- Non-compliance with clinical study regulations by the study subject

Efforts will be made to obtain information on patients who discontinue the clinical study, and the reasons for discontinuation of treatment or observation will be recorded. For study subjects whose participation is discontinued, follow-up may continue with patient consent. However, in the event of withdrawal of consent, follow-up will not be conducted, and patients who discontinue participation in the clinical study will not be replaced.

At any time during the clinical study, if a serious adverse event or an adverse reaction deemed harmful to the

study subject is observed, and if subsequent evaluation of the course and causality of the adverse event with the treatment determines that continuation of treatment is harmful to the study subject, the investigator will permanently discontinue the treatment for the patient in this clinical study.

- Study subjects who discontinue before starting treatment are considered screening failures. Unless medically necessary, all required assessments at the time of discontinuation (screening failures) do not have to be completed.
- Subjects who withdraw early due to adverse events may receive appropriate treatment for the adverse events if necessary. In the case of early withdrawal due to adverse events, the investigator or an investigator designee must continuously evaluate the study subject until the adverse event resolves or is deemed permanent.

Other reasons for discontinuation of the clinical study by the investigator include:

- If a disease that could affect the outcome of the study is discovered in the study subject that was not detected in pre-study screening.
- If there are issues performing medical procedures for temporomandibular joint disease in the study subject.

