### **3.5. Sample size calculation**

Calculation of the number of clinical study subjects: As this study is an investigator-initiated clinical trial, the sample size was determined by referencing existing similar studies and clinical experience..

- 1) Level of significance,  $\alpha=0.05$ (two-tailed test)
- 2) Type II error ( $\beta$ ) is set at 0.2, making the power of the test 80%.
- 3) There is no existing study comparing Korean Chuna therapy and usual care for TMJ-related conditions in Korea. Therefore, based on clinical experience and manual therapy studies in China 1-3), the effect size for comparing the mean differences in pain VAS between the two groups is assumed to be at least medium (effect size = 0.7).
- 4) G\*Power 3.1.7 is used to calculate the sample size.

Assuming an effect size of 0.7, 34 subjects per group (a total of 68 subjects) are required. However, since the main analysis will be performed using ANCOVA, adjusting for baseline outcome values, and assuming a correlation value of 0.3 between baseline and the primary endpoint, the sample size is calculated as  $(1 - 0.3 * 0.3) * 68$ , resulting in 62 subjects. Considering a 30% dropout rate during the study, a total of 80 subjects will be recruited, with 40 subjects per group.

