## 6. Outcomes

### 6.1. Primary outcomes

#### Visual Analogue Scale (VAS) for TMJ pain

VAS will be evaluated on the 1st, 3rd, 5th, and 7th treatment visits (week 1–4) and 5 weeks, 3 months, and 6 months after allocation. The average TMJ pain for the past week will be investigated. The primary endpoint is VAS at 5 weeks after allocation (a week after the last treatment). The far left end of a 100 mm scale line means “no pain” and the far right end means “the worst pain imaginable.” It is the most frequently used way to measure the pain severity. A participant puts a mark on the line, which approximates his/her own pain for the past week. If a participant complains of different pain levels on each TMJ, the more severe side will be recorded.

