#### **6.3.2 General principles of analysis**

- This study analyzes the results of pain intensity scale, functional scale, quality of life, and cost data for patients who meet the inclusion criteria in a randomized controlled trial.
- The primary analysis will use the ITT (Intention-to-Treat) approach, evaluating all subjects who received at least one treatment. Additionally, the PP (Per-Protocol) analysis will be conducted alongside, evaluating only those subjects who completed the clinical study without dropping out. Missing data will be handled primarily through Multiple Imputation, and LOCF (Last Observation Carried Forward) will be used for sensitivity analysis.
- The socio-demographic characteristics and treatment expectancy of the study subjects will be evaluated by group. Continuous variables will be expressed as mean (standard deviation) or median (interquartile range) and compared between the two groups using Student's t-test. Categorical variables will be expressed as frequency (%) and analyzed using the chi-square test or Fisher's exact test.
- The efficacy evaluation variables of this clinical study are the differences in the changes of continuous outcomes (VAS, NRS, MMO, K-BDI-2, JFLS, SF-12, EQ-5D-5L, EQ-VAS) between the two groups from baseline to each time point. ANCOVA (Analysis of Covariance) will be performed with the baseline values of each variable and the covariate factors that show statistical differences between the

treatment groups at baseline as covariates, and the group as a fixed factor. RM ANOVA (Repeated Measures ANOVA) will be conducted to test the differences in trends at each visit.

- To compare the total amount of differences in each outcome within the period (evaluation time point after treatment completion (5 weeks)) and the entire study period (6 months), the areas under the curve (AUC) at each time point after randomization will be calculated and compared using Student's t-test.

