### 1.1 General principles of analysis

- This study analyzes the results of pain intensity scale, functional scale, quality of life, and cost data for patients who meet the inclusion criteria in a randomized controlled trial.
- The primary analysis will use the ITT (Intention-to-Treat) approach, evaluating all subjects who received at least one treatment. Additionally, the PP (Per-Protocol) analysis will be conducted alongside, evaluating only those subjects who completed the clinical study without dropping out. Missing data will be handled primarily through Multiple Imputation, and LOCF (Last Observation Carried Forward) will be used for sensitivity analysis.
- The socio-demographic characteristics and treatment expectancy of the study subjects will be evaluated by group. Continuous variables will be expressed as mean (standard deviation) or median (interquartile range) and compared between the two groups using Student's t-test. Categorical variables will be expressed as frequency (%) and analyzed using the chi-square test or Fisher's exact test.
- The efficacy evaluation variables of this clinical study are the differences in the changes of continuous outcomes (VAS, NRS, MMO, K-BDI-2, JFLS, SF-12, EQ-5D-5L, EQ-VAS) between the two groups from baseline to each time point. ANCOVA (Analysis of Covariance) will be performed with the baseline values of each variable and the covariate factors that show statistical differences between the treatment groups at baseline as covariates, and the group as a fixed factor. RM ANOVA (Repeated Measures ANOVA) will be conducted to test the differences in trends at each visit.
- To compare the total amount of differences in each outcome within the period (evaluation time point after treatment completion (5 weeks)) and the entire study period (6 months), the areas under the curve (AUC) at each time point after randomization will be calculated and compared using Student's t-test.

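### LOCF is the protocol's only missing-data sensitivity analysis, and nothing in the document examines graded departures from the missing-at-random assumption usual for multiple imputation

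*Protocol*

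**What the plan says.** Protocol section 6.3.2 (General principles of analysis) sets the rule: "Missing data will be handled primarily through Multiple Imputation, and LOCF (Last Observation Carried Forward) will be used for sensitivity analysis". The statistical methods section at the end of the document repeats it under 1.1 ("Missing data will be handled primarily through Multiple Imputation, and LOCF") and adds nothing to it.

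The main analysis set is described as ITT, "evaluating all subjects who received at least one treatment". A per-protocol analysis runs beside it, "evaluating only those subjects who completed the clinical study without dropping out".

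On the amount of missing data, section 3.5 says: "Considering a 30% dropout rate during the study, a total of 80 subjects will be recruited, with 40 subjects per group". Under section 3.4, for a patient who discontinues, "follow-up may continue with patient consent"; after withdrawal of consent there is none.

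The primary endpoint (section 6.1) is self-reported VAS at Week 5, one week after the last treatment. VAS is also recorded once a week in Weeks 1 to 4, at the first visit of the week. Section 5.2.2 blinds only the assessors.

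**The concern.** Standard multiple imputation usually assumes that, given the observed data, patients with missing values resemble those who stayed (missing at random, MAR). The protocol does not state this assumption; it is inferred from the method. A missing-data sensitivity analysis should show how far the missing patients would have to depart from that assumption before the conclusion changes.

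The protocol chooses LOCF for this role. LOCF holds a dropout's pain at the last recorded value, from baseline or mid-treatment, and treats it as if observed at Week 5. That is implausible while pain is changing, and as single imputation it understates uncertainty.

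The question is a practical one here. Patients know their treatment and rate their own pain. Section 5.5.3 bars other TMJ treatment until Week 5, and section 3.4 lists certain outside treatment taken without direction as a ground for discontinuation, after which follow-up is optional. A patient whose pain persists could therefore be lost for a reason tied to the outcome. The documents do not say how often this is expected.

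**Working it through.** **The plan's own figures.** With effect size 0.7 and two-sided alpha 0.05, the t-test has 79.97% power at 33 per group and 81.2% at 34, so 34 per group (68) reproduces. The ANCOVA factor gives (1 - 0.3²) × 68 = 61.88, i.e. 62. The planned dropout is 0.30 × 80 = 24 patients. How 62 becomes 80 is a separate matter and does not affect this point.

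**What LOCF does (assumed inputs).** The documents give no pain trajectory. Assume straight lines from Week 1 to Week 5:
- Usual care: 60, 56.25, 52.5, 48.75, 45 mm
- Chuna: 60, 53.75, 47.5, 41.25, 35 mm
- True Week-5 difference: 35 - 45 = -10 mm

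Let dropout be unrelated to outcome within arm, with the last value equally likely to be from any of Weeks 1 to 4. The mean carried-forward values are 54.375 mm (usual care) and 50.625 mm (Chuna).

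LOCF arm mean = (1 - p) × Week-5 mean + p × mean carried forward.

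| Dropout, usual care / Chuna | Usual care mean | Chuna mean | LOCF difference |
|---|---|---|---|
| 30% / 30% | 47.8125 | 39.6875 | -8.125 |
| 20% / 40% | 46.875 | 41.25 | -5.625 |
| 30% / 10% | 47.8125 | 36.5625 | -11.25 |
| 10% / 10% | 45.9375 | 36.5625 | -9.375 |

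Timing matters by itself. At 30% / 30%, if every dropout's last value is from Week 1, LOCF gives (0.7 × 35 + 0.3 × 60) - (0.7 × 45 + 0.3 × 60) = 42.5 - 49.5 = -7.0 mm. If every last value is from Week 4, it gives 36.875 - 46.125 = -9.25 mm.

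**LOCF as a hidden shift.** Relative to the Week-5 arm means, LOCF makes usual-care dropouts 54.375 - 45 = 9.375 mm worse and Chuna dropouts 50.625 - 35 = 15.625 mm worse. So:

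LOCF difference = -10 + 15.625 × p(Chuna) - 9.375 × p(usual care)

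This reproduces the table. It is a single point on a delta grid, and the trajectory and timing choose it, not the analyst.

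- *Disagreement while MAR holds:* MAR holds in every row above, so a correctly specified imputation by arm would centre on -10 mm. LOCF does not.
- *Agreement while MAR fails:* at 30% usual care / 18% Chuna the two terms cancel (0.18 × 15.625 = 0.30 × 9.375 = 2.8125) and LOCF gives -10. If the Chuna dropouts' unseen Week-5 values were in fact 20 mm worse than MAR predicts, the true difference would be -10 + 0.18 × 20 = -6.4 mm. LOCF and multiple imputation would still both give -10, because neither sees those values.

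**What a delta analysis would show (illustrative).** Assume 40 per arm, m observed per arm, SE = √(2/m) × √0.91 in SD units, t with 2m - 3 df, and a shift applied only to missing Chuna patients. The tipping shift is (estimate - t × SE) / proportion missing.

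| Missing | m | SE | t × SE | Estimate 0.7 | Estimate 0.6 | Estimate 0.5 |
|---|---|---|---|---|---|---|
| 30% | 28 | 0.255 | 0.511 | 0.63 SD | 0.30 SD | not significant under MAR |
| 22.5% | 31 | 0.242 | 0.485 | 0.96 SD | 0.51 SD | 0.07 SD |
| 10% | 36 | 0.225 | 0.449 | 2.51 SD | 1.51 SD | 0.51 SD |

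The documents give no SD for VAS. With an assumed 15 to 25 mm, 0.63 SD is about 9 to 16 mm.

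**The case against.** The strongest reply is that LOCF makes a different assumption from MAR and, when pain is falling, gives dropouts a worse value than their arm's completers. It is therefore not empty, and with equal dropout it only attenuates (-8.1 against -10 mm). That stands, and it would be too strong to call LOCF uninformative. But it is one fixed and unstated departure, not a graded one, and unequal dropout can push it the other way. The 30% / 10% split that does so is assumed; the documents predict no imbalance.

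A reader might infer that 24 of 80 will be missing at the primary endpoint. The documents do not support this. Section 3.5 speaks of dropout during the study, which runs to 6 months, so Week-5 missingness may be well below 30%. Continued follow-up with consent and permitted rescue medication may lower it further. At 10% missing, an estimate of 0.7 SD is robust to any plausible shift.

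A reader might also say that MAR goes untested. It cannot be tested from observed data by any method, a tipping-point analysis included. What is lacking is an examination of departures from it.

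Nor does the criticism extend to the repeated-measures analysis ("RM ANOVA (Repeated Measures ANOVA) will be conducted to test the differences in trends at each visit"). Section 6.3.2 does not exempt it from multiple imputation, and a mixed model in its place would also rest on MAR.

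Finally, a separate statistical analysis plan may exist, and imputation models and delta grids commonly belong there. Their absence from the protocol is not the complaint. The complaint is that the protocol itself names LOCF as the check.

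**Conclusion.** The point holds in a limited form. LOCF is the only missing-data sensitivity analysis named, and no analysis in this document examines graded departures from MAR. The per-protocol analysis does not fill the gap, since it drops the patients in question. LOCF can move the estimate either way: -5.6 to -11.3 mm around a true -10 mm, under assumed linear paths and assumed dropout splits. Its agreement or disagreement with multiple imputation says nothing definite about MAR.

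How much this matters depends on Week-5 missingness. At the 30% upper scenario, an estimate of 0.6 to 0.7 SD would lose significance if missing Chuna patients were 0.30 to 0.63 SD worse than MAR predicts; at 10% the shift would have to be 1.51 to 2.51 SD. These figures use an approximate standard error and a shift in one arm only.

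It would go too far to infer that the primary analysis is biased. Multiple imputation is a sound primary choice, and the illustration shows error in LOCF, not in the primary result. This is an inexpensive improvement to the robustness check.

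**What to change.** In section 6.3.2, and in the matching text in section 1.1 of the appended statistical methods, replace LOCF as the sensitivity analysis, or keep it as supplementary only. Specify a delta-adjusted tipping-point analysis on the planned multiple imputations of Week-5 VAS:

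- Shift the imputed values separately by arm over a grid fixed in advance, for example 0 to 20 mm. That range is an assumption, and the sponsor should justify its own.
- Repeat the ANCOVA at each point of the grid, and report the estimates and the shift at which significance is lost.
- Report missing Week-5 VAS by arm, with reasons, so that the tipping shift can be judged for plausibility.

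The cost is a grid to pre-state, a few lines of code on imputations already planned, and one more table. Design, sample size and patient care do not change.

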## **5. Method**

### **5.1. Design**

The study design is a 2-arm parallel multicenter RCT (Kyung Hee University Hospital of Korean Medicine, Gangdong, Jaseng Hospital of Korean Medicine (Gangnam), Daejeon Jaseng Hospital of Korean Medicine, Bucheon Jaseng Hospital of Korean Medicine, Haeundae Jaseng Hospital of Korean Medicine). Study participants will receive outpatient treatment for a total of 4 weeks. After screening at the initial visit, participants who meet the inclusion/exclusion criteria will be randomly assigned to either the Chuna manual therapy group (40 participants) or the usual care group (40 participants). Treatment for temporomandibular joint (TMJ) pain disorders will be administered according to the developed clinical study protocol.

For the economic evaluation study, cost data collection and utility assessment for estimating QALY (Quality Adjusted Life Year) will be conducted. During the clinical study period, quality of life will be assessed using EQ-5D, EQ-VAS, and SF-12 measurement tools at Visits 2, 10, and 12. Various costs will be assessed using developed survey items at the first visit of each week. Additionally, a separate follow-up survey will be conducted until 6 months (Visit 12) after clinical study enrollment. The survey will be conducted through face-to-face interviews, telephone interviews, or distributed questionnaires, measuring healthcare utilization and quality of life.

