#### Short Form-12 Health Survey (SF-12), version 2.

SF-12 will be conducted on the 1st treatment visit, prior to the treatment, a week after the last treatment, and at the 3-month and 6-month follow-ups. It contains 12 items about health-related quality of life. A higher total score reflects a better quality of life.

5-Level EuroQol-5 Dimension (EQ-5D-5 L) and EuroQol Visual Analogue Scale (EQ-VAS).

EQ-5D-5 L and EQ-VAS will be conducted on the 1st treatment visit, just before the treatment, a week after the last treatment, and at the 3-month and 6-month follow-ups. The EQ-5D-5 L evaluates health state, and the total score is indirectly calculated through a specifically developed equation. It is composed of five items (mobility, self-care, usual activities, pain, and anxiety/ depression). EQ-VAS uses a 100 mm line, which ranges from the worst health condition on the left end to the best health condition on the right end. Participants will be asked to mark the point corresponding to one's own health condition on that day.

Cost data investigation

Cost data include medical consumption, non-medical consumption and productivity loss cost of societal perspective. A questionnaire will be developed to evaluate consumption profiles, such as formal/informal medical consumption, non-medical consumption, and time consumption. While formal medical consumption refers to medical interventions and drugs, informal medical consumption refers to health food, medical instruments, etc. Non-medical consumption includes the cost of transportation, time consumption, and nursing. The Work Productivity and Activity Impairment questionnaire (WAPI) will be used for the cost of productivity impairment [24]. Medical consumption and non-medical consumption will be investigated with questionnaires which contains the cost data and the received treatment of participants and the cost data of Korean National Health Insurance will also be analyzed to calculate consumptions.

Credibility and expectancy questionnaire

The 9-point Likert scale for Credibility and Expectancy This scale is used to assess the participants' expectancy of the trial. On the 1st treatment visit, before the treatment, they will be asked how much the symptom would be reduced by the CMT and UC (1=not at all, 5=somewhat, and 9=very much).

Adverse events

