### 6.3.3. Economic evaluation

Economic evaluation will be implemented to compare the cost-effectiveness of CMT and UC. The primary economic endpoint will be an incremental cost-effectiveness ratio (ICER) of CMT compared with UC. ICER will be obtained by incremental cost between CMT and UC divided by incremental effectiveness between CMT and UC. Accordingly, additional cost will be calculated when 1 QALY is increased [26]. If predictions about subsequent periods are needed, cost and effectiveness after follow-up period will be extrapolated using regression models or secondary analysis such as decision modelling analysis. The treatment cost of this trial will be calculated by considering the number of treatments and their unit cost, derived from the health insurance cost and the agency cost. QOL inferred from the EQ-5D-5 L will be the primary measurement for the assessment of QALY, and the AUC method will be used [18]. If the total time horizon is more than 12 months, the cost unit will be standardized as the Korean currency (won), and a discount rate of 5% will be applied, based on the guidelines for economic assessment of the Health Insurance Review & Assessment Service. This analysis will be conducted from the societal perspective. Representative values (i.e. mean) of parameters will be used in the baseline analysis. Sensitivity analysis will be carried out in the form of probabilistic sensitivity analysis by using the distribution of all possible parameters and their representative values. In order to confirm the robustness of the analysis results, the probabilistic sensitivity analysis will be performed by setting the range of cost, effect and transition probability variable to 95% confidence interval. The utility weight and the transition probabilities will be analyzed with the triangular distribution and the cost data will be analyzed with the normal distribution for the distribution of the variable. Monte Carlo simulation will be performed 10,000 times and the mean and 95% confidence interval will be calculated. After conducting probabilistic sensitivity analysis, cost-effectiveness acceptability curve will be confirmed [27].

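### The 5-week and 6-month AUCs are compared by an unadjusted t-test, although the same outcomes are baseline-adjusted at each visit: a loss of precision that costs nothing to correct

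*Protocol*

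**What the plan says.** Protocol 6.3.2 sets two methods for the same continuous outcomes.

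- By time point: "ANCOVA (Analysis of Covariance) will be performed with the baseline values of each variable", with group as fixed factor. The listed outcomes include VAS, NRS, JFLS, SF-12, EQ-5D-5L and EQ-VAS.
- Over the period to week 5 and over the whole 6 months: "the areas under the curve (AUC) at each time point after randomization will be calculated and compared using" Student's t-test. No covariate is named.

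Section 1.1 of the Statistical Analysis Methods appended to the protocol repeats both.

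For the economic evaluation, Protocol 6.3.3 (repeated in appended section 1.2) says: "QOL inferred from the EQ-5D-5 L will be the primary measurement for the assessment of QALY, and the AUC method will be used". It then says: "ICER will be obtained by incremental cost between CMT and UC divided by incremental effectiveness between CMT and UC". Whether the incremental QALY is adjusted for baseline utility is neither stated nor excluded.

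On when quality of life is measured, Protocol 5.1 says: "quality of life will be assessed using EQ-5D, EQ-VAS, and SF-12 measurement tools at Visits 2, 10, and 12". Section 6.2 places EQ-5D-5L, EQ-VAS and SF-12 at the first treatment visit, then "a week after the last treatment, and at the 3-month and 6-month follow-ups", and the timetable agrees with 6.2.

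**The concern.** An AUC over repeated visits is a weighted mean of those visits, so it correlates with the baseline value at least through the later measurements, and directly if baseline is its first point. The plan recognises the value of baseline elsewhere. Section 3.5 calls ANCOVA the main analysis and uses a baseline correlation of 0.3 to reduce the required sample. Dropping the covariate for the AUC of the same outcomes, with no reason given, has two consequences. The confidence interval is wider than the collected data allow. And with 40 patients per arm, a chance difference at baseline carries over into the AUC difference, so the AUC and by-visit results for one outcome could point different ways for that reason alone.

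The QALY is also an AUC, and it forms the denominator of the primary economic endpoint, so the same question arises there.

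**Working it through.** **The plan's own figure.** The documents give no figure for the AUC comparison. The one figure that uses baseline is in 3.5: (1 − 0.3 × 0.3) × 68 = 61.88, rounded up to 62. This reproduces. It implies a 9% variance reduction (0.3² = 0.09) at a single visit.

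**Inputs for the AUC.**
- Baseline to any later visit: correlation 0.3. This is the plan's value for the primary endpoint, applied here to all visits.
- Among later visits: correlation ρ = 0.5 to 0.7 (assumed).
- Equal variances at all visits (assumed, set to 1).
- VAS times: weeks 1 to 5, then 3 and 6 months after the first Week 1 visit (timetable), taken as weeks 14 and 27. The first treatment visit is taken as baseline.

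**Formula.** With trapezoid weights w scaled to sum to 1 and w₀ on baseline:
- Cov(AUC, baseline) = w₀ + 0.3(1 − w₀)
- Var(AUC) = w₀² + 2 × 0.3 × w₀(1 − w₀) + ρ(1 − w₀)² + (1 − ρ)Σwⱼ², summed over later visits
- Share of variance removed by adjustment = Cov² / Var

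**To week 5, baseline included.** Weights are 0.125, 0.25, 0.25, 0.25, 0.125.
- Cov = 0.125 + 0.3 × 0.875 = 0.3875, squared 0.1502.
- Var = 0.5656 at ρ = 0.5 and 0.6781 at ρ = 0.7.
- Removed: 26.5% and 22.1%. The standard error falls to 0.86–0.88 of its unadjusted value.

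**To 6 months, baseline included.** Weights (over 26) are 0.5, 1, 1, 1, 5, 11, 6.5, so w₀ = 0.019.
- Cov = 0.3135, squared 0.0983.
- Var = 0.6341 and 0.7699.
- Removed: 15.5% and 12.8%. Standard error ratio 0.92–0.93.

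**Baseline left out of the AUC.** Cov = 0.3, squared 0.09.
- To week 5: weights 1/6, 1/3, 1/3, 1/6; Var = 0.6389 and 0.7833; removed 14.1% and 11.5%.
- To 6 months: removed 13.8% and 11.4%.

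**How likely imbalance is.** With 40 per arm the baseline mean difference has standard error √(2/40) = 0.224 SD. The probability that it exceeds 0.2 SD in either direction is 37%; the 95% range is ±0.44 SD. Given an imbalance δ and AUC–baseline correlation r, the unadjusted test statistic is about normal with mean rδ/0.224 and variance 1 − r². For r = 0.5 and δ = 0.44 the mean is 0.98 and the SD 0.866, giving a conditional type I error of about 13%. For δ = 0.2 it is about 4%.

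**QALY.** Trapezoid weights in years at weeks 0, 5, 13 and 26 are 0.048, 0.125, 0.202 and 0.125. For an assumed baseline utility imbalance of 0.03 and the plan's correlation of 0.3, the expected shift without adjustment is 0.03 × (0.048 + 0.3 × 0.452) = 0.0055 QALY. Counting time from Week 1 instead gives 0.03 × (0.0385 + 0.3 × 0.4615) = 0.0053. If the imbalance persisted in full it would be 0.03 × 0.5 = 0.015.

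**Visit list.** Visit 2 is the first Week 1 visit (timetable footnote), Visit 10 is week 5 (5.5.3) and Visit 12 is 6 months (5.1), so Month 3 is Visit 11. It is in the timetable and 6.2 for all three instruments and absent from the list in 5.1. Month 3 carries the largest QALY weight, 0.202 of 0.5 year.

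**The case against.** Several points on the other side stand.

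- A reader might infer that the t-test is biased or has an inflated error rate. It does not. Under randomisation it is unbiased on average and keeps its overall 5% type I error; the 13% above is conditional on an imbalance at the edge of the 95% range.
- A reader might infer that baseline is discarded. It is unused only as a covariate in the AUC test. It may still be the first AUC point, and it enters the ANCOVA of the same outcomes at each visit.
- The text does not say whether the AUC starts at baseline, which is why two sets of figures are given. For JFLS, K-BDI-2, SF-12, EQ-5D-5L and EQ-VAS the timetable has only two points up to week 5, so a 5-week area for those outcomes needs baseline, at half the weight. For VAS to 6 months baseline carries only 1.9%.
- A reader might infer that the ICER will be formed from unadjusted QALYs. The economic section does not say so. Its reference to means in the base case does not settle whether they are adjusted, and a separate analysis plan could specify this. The QALY part is therefore secondary.
- A reader might infer that the QALY will omit Month 3. Nothing says that. The timetable and 6.2 both schedule it, and 5.1 itself adds a follow-up survey of quality of life to 6 months.

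What remains is the explicit, twice-stated choice of an unadjusted test for the AUC. None of these points supplies a reason for it.

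**Conclusion.** The concern holds as a matter of efficiency and consistency. The plan fixes an unadjusted t-test for the AUCs where its own ANCOVA form would do better with data already in hand. The gain is about 22–27% of AUC variance at 5 weeks and 13–16% at 6 months for VAS with baseline as the first AUC point, or about 11–14% with baseline left out. These figures rest on the plan's correlation of 0.3 applied to every later visit, an assumed 0.5–0.7 among later visits, and equal variances.

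The week-5 VAS, the primary endpoint, is already baseline-adjusted and is untouched. For QALYs the documents are silent, and a 0.03 utility imbalance would shift the 6-month difference by about 0.005 under the plan's correlation. The figure of 0.015 requires full persistence, which does not fit a correlation of 0.3. The visit list in 5.1 is a real contradiction but needs only a wording correction.

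**What to change.** In Protocol 6.3.2 and in section 1.1 of the appended Statistical Analysis Methods, replace the t-test for the AUCs with linear regression (ANCOVA) of each AUC on group, with that outcome's baseline value as covariate. State whether baseline is the first AUC point.

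In Protocol 6.3.3 and appended section 1.2, state that incremental QALYs are estimated by regression on group and baseline EQ-5D-5L utility, using all four measurement points (Visits 2, 10, 11 and 12).

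In 5.1, reconcile the visit list for EQ-5D, EQ-VAS and SF-12 with the timetable and 6.2, which include Month 3.

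The cost is a change of wording. No new data, visits or patients are needed.
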